### Statistical analysis

IBM SPSS (Version26, Chicago, USA) will be used for statistical analysis. If the continuous variable is normally distributed, it will be presented as the mean (standard deviation, SD) with t-tests, or as the median (interquartile range, IQR) with Mann-Whitney U tests if it is not. Categorical variables will be provided as frequency (N) with percentage (%) and assessed using the chi-square or Fisher’s exact test. The Kaplan–Meier curves with the log-rank test will be used to compare the groups’ survival. A bilateral *p*-value of 0.05 or less is deemed to be statistically significant.

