### Study population

The clinical efficacy of the TH and RTA approaches for the resectable ST-II AGE, which is the aim of the study. The eligibility of all patients will be determined by their surgeon.

The inclusion criteria are described briefly below:Aged 18–75;Histologically confirmed as Siewert type II AEG;Clinical stage ranges cT1-4aN0-3 M0 (According to the 8th AJCC TNM staging system) and is confirmed by the preoperative examinations (Gastroscopy, enhanced or not computer tomography (CT), magnetic resonance imaging (MRI) or positron emission tomography with CT (PET-CT)).The operation will be performed by either TH or RTA approach according to the direction of the research center and the surgeon;American Society of Anesthesiologists (ASA) physical status score of 1–3;Eastern Cooperative Oncology Group (ECOG) performance status of 0–1;Laboratory test criteria: hemoglobin > 90 g/L, white blood cell > 3 × 10^9/L, platelets > 100 × 10^^9^/L, serum albumin (ALB) > 30 g/L, renal function (serum creatinine (Scr) < 1.5 × ULN and glomerular filtration rate > 60 ml/min), and liver function (alanine transaminase (ALT) and aspartate transaminase (AST) less than 2.5× upper limit of normal);Informed consent of patients is required.

The exclusion criteria are as follows:Siewert type I or III AEG;Postoperative pathological types confirmed as non-adenocarcinoma or non-simple adenocarcinoma;Distant metastasis (M1) or invasion of the peritoneum;Clinically significant central nervous system disease that may influence compliance;Clinically significant diseases (Irregularly controlled diabetes and hypertension; History of myocardial infarction or cerebral infarction within 6 months before the operation; Heart function: New York Heart Association (NYHA) class II or higher; Respiratory function: Forced expiratory volume in the first second (FEV1) < 50%; Liver function: Child-Pugh class C; Renal function: Serum creatinine (Scr) > 1.5xULN and glomerular filtration rate < 60 ml/min;History of gastrectomy (including endoscopic mucosal resection or submucosal dissection);Diagnosed with other malignancies within 5 years;Pregnancy or breast-feeding;Tumor-related complications (dysphagia, gastrointestinal bleeding, perforation, obstruction, etc.) requiring emergency surgery;Being assessed by the investigator as unsuitable for the trial;Persistent withdrawal from clinical trials.

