### Patient screening

The flow chart of this research is presented in Fig. 1. Multidisciplinary evaluation and standard clinical staging will be done for each patient before enrollment. Based on the anatomical location of the tumors revealed by gastroscopy and the results of the pathological examination of biopsy tissues, the tumors will be classified according to Siewert classification. Imaging examinations (CT, enhanced CT, MRI or PET-CT) will be conducted for determining whether the tumor has distal metastasis and invasion. Complete preoperative preparation also includes anamnesis, demographic information, physical examination, vital signs and laboratory tests.

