### Inclusion and randomization of patients

On the completion of the baseline assessment and clinical staging, the criteria for inclusion and exclusion will be validated. Informed consent of all participants must be obtained in this trial. Subsequently, the participants will be further divided into the TH cohort or the RTA cohort in a ratio of 1:1 according to the computer-generated random numbers. Then these participants will receive the operation within 1 week after randomization.

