### Data collection and management

When a patient is included in the study, a randomized number will be generated and applied in the database. The patient’s codes are accessible to PI and COI. The study coordinator will collect the clinical data and record it on a unique clinical case report form. Each center assigns a dedicated person responsible for the randomization of the enrolled patients, data entry, proofreading, uploading, etc. The final data is summarized in the central database. Data quality inspectors will regularly inspect and control the quality of data entry and database management.

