### Intervention

Depending on randomization results, patients will undergo either the TH or the RTA approach operation. The technical details of both approaches are determined based on the preferences of individual surgeons, on the condition of achieving the key goal of completely tumor resection. Minimally invasive surgery and robotic surgery are allowed if the technology and equipment at the local research center are supported. However, if the tumor cannot be completely removed, the surgeons should promptly change their surgical strategy.

Proximal or total gastrectomy with standard D2 lymphadenectomy will be achieved by the transabdominal approach in the TH group. Distal esophagectomy and mediastinal lymphadenectomy will be done through the transhiatal approach. In the RTA group, the intra-abdominal procedure is the same as in the TH group. In addition, an oblique incision over the right thorax will be made, and esophagectomy and mediastinal lymphadenectomy will be completed through the right transthoracic approach.

Reconstruction methods should be determined by the attending physician based on experience and patients’ individual conditions during the operation. Proximal gastrectomy can be followed by gastric tube construction and esophagogastrostomy. It is recommended that the Roux-en-Y (esophagojejunostomy and jejunojejunostomy) reconstruction will be done following the total gastrectomy.

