### Outcome measurements

The primary endpoint of the study is the 3-year DFS. DFS is the timeframe between the operation and recurrence, progression, or death.

The secondary endpoint:3-year overall survival (OS): OS is the time from operation to death due to any cause or the last follow-up.R0-resection: Patients who undergo radical resection without positive margins;Number and station of lymph nodes (LNs): Detected in postoperative specimens;Postoperative mortality: Death within 30 days after surgery;Duration of postoperative hospitalization: The time from the operation to discharge;Postoperative complications: Postoperative complications include respiratory complications (postoperative pneumonia, pleural effusion, pulmonary insufficiency), cardiac complications (acute myocardial infarction, heart failure, arrhythmia), intra-abdominal bleeding, intra-abdominal abscess, anastomotic structure, anastomotic leakage, chyle leakage, deep venous thrombosis, and wound infection. All postoperative complications will be classified according to the Clavien-Dindo grading system [27];Quality of life (QOL): Using the European Organization for Research and Treatment of Cancer Quality of Life questionnaire (EORTC: QLQ-C30, QLQ-STO22, and QLQ-OG25 after 3, 6, 9, 12, 18, 24, and 36 months).

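### The stated log-rank test for DFS names no stage strata, although clinical stage is known for every patient before randomisation; it is valid but may give up some power

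*Protocol article*

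**What the plan says.** All of the following is in the protocol article.

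- Outcome measurements: "The primary endpoint of the study is the 3-year DFS", timed from the operation.
- Statistical analysis: the "log-rank test will be used to compare" the two groups on survival, with Kaplan–Meier curves. DFS is not mentioned by name, and no other survival method is given.
- Inclusion and randomization of patients: allocation is "in a ratio of 1:1 according to the computer-generated random numbers". No stratification factor is named.
- Study population: "Clinical stage ranges cT1-4aN0-3 M0".
- Patient screening: "Multidisciplinary evaluation and standard clinical staging will be done for each patient before enrollment".

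**The concern.** Eligible tumours range from early to locally advanced, so the hazard of recurrence or death may differ a good deal between patients within each arm. A plain log-rank treats all of them as one risk set. If stage is prognostic, this has two effects. The overall hazard ratio lies closer to 1 than the ratio among patients of the same stage, and the test has less power than one that compares patients within stage.

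The direction matters in this trial. The Objective and Discussion sections expect the two approaches to give equivalent survival. Loss of power makes a non-significant result more likely, and such a result could be read as support for that expectation.

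Clinical stage is well suited to stratification. It is recorded for everyone, it is fixed before allocation, and it cannot be altered by the surgical approach.

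**Working it through.** **Inputs from the Sample size calculation section:** 3-year DFS 41.5%; difference 0.07; two-sided 5% type I error; 80% power; 10% dropout; 156 per arm. Evaluable per arm: 156 × 0.90 = 140.4, taken as 140.

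**Step 1: the plan's own figure.** For two proportions, n per arm = [1.960·√(2·0.45·0.55) + 0.842·√(0.415·0.585 + 0.485·0.515)]² / 0.07² = (1.379 + 0.591)² / 0.0049 ≈ 792, or 792/0.9 = 880 after dropout. For the log-rank, HR = ln 0.485 / ln 0.415 = 0.823. Events = 4·(1.960 + 0.842)² / (ln 0.823)² ≈ 825, and 825/0.55/2 = 750 per arm before dropout. The stated 156 is not reproduced. That is a separate problem, but it sets the power from which any gain starts.

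**Step 2: power of the plain log-rank at 140 per arm.** Expected events = 280 × 0.55 = 154. Power = Φ(½·√154·|ln 0.823| − 1.960) = Φ(1.210 − 1.960) ≈ 23%.

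**Step 3: simulation of plain and stage-stratified log-rank tests.** Hazards are exponential and follow-up is cut at 3 years. Allocation is unstratified 1:1. Hazards are set so that 3-year DFS over all stages stays at 41.5% and 48.5%. There are 6,000 replicates per row, so the simulation standard error is √(0.25·0.75/6000) ≈ 0.6 points.

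Assumptions that are not in the documents: three equal stage groups, the log hazard ratio per stage step (varied below), 8 centres, and a centre standard deviation of 0.2 on the log hazard.

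| Log-HR per step | HR per step (exp) | Plain | Stage-stratified | Gain (points) | Repeat run: plain / stratified |
|---|---|---|---|---|---|
| 0 | 1.00 | 22.4% | 22.5% | 0.1 | 22% / 22% |
| 0.4 | 1.49 | 23.1% | 24.6% | 1.5 | 24% / 24% |
| 0.7 | 2.01 | 24.4% | 29.2% | 4.8 | 23% / 28% |
| 1.0 | 2.72 | 23.7% | 34.3% | 10.6 | 25% / 34% |

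The same section also gives a recruitment total of 356. That is 178 per arm, or about 160 evaluable. Plain power is then 25.7–27.0%, and stage-stratified power is 25.8%, 28.2%, 31.5% and 38.2% over the same four rows.

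**Step 4: validity.** With no true difference and 140 per arm, the plain test rejected in 4.9–5.4% of replicates and the stage-stratified test in 4.9–5.8%. Both are close to the nominal 5%.

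**Step 5: centre as a stratum.** At 140 per arm and 8 centres, stratifying by centre alone gave 22.6–23.8%, no better than the plain test. Crossing stage with centre gave 20.6%, 22.9%, 26.9% and 30.8%, below stage alone in every row. With 20 centres and a log-HR of 0.7 per step, the plain test had 23.8%, stage 26.8%, centre 21.8%, and stage by centre 21.2%.

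**The case against.** The strongest reply is that nothing here is stated wrongly. A plain log-rank is valid and matches the allocation as described, and chance imbalance in stage is already covered by its 5% error rate. The article is a condensed account: it does not call the test unadjusted, and it does not exclude strata or a Cox model in a fuller plan. The prognostic strength of stage is an assumption, and in the first two rows of the table the gain is nil or negligible.

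All of that stands, and it limits the point to a recommended improvement. The article does, however, name a specific test for survival. For that test a better alternative uses data already held and costs essentially no power in the simulated settings even if stage predicts nothing.

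A reader might infer more, and the documents do not support it:

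- *That stage information is being thrown away, or that the result will be biased.* The article is silent on adjustment and does not refuse it, and the type I error holds.
- *That centre should be a stratum too.* The number of centres is not given, and under the assumed centre effect centre strata brought no gain and could cost power.
- *That surgical skill is mixed with approach.* "The technical details of both approaches are determined based on the preferences of individual surgeons", but the Study design section requires surgeons competent in both approaches. The Management and quality control section adds a minimum of 20 cases, a qualification examination and review of operative photographs.
- *That allocation was simple and should now be stratified.* The article does not say so. It states that "Each center assigns a dedicated person responsible for the randomization of the enrolled patients", which leaves allocation by centre open. Enrolment began in late 2019 and was planned for about 3 years, so such a change may come too late.
- *That stratification would carry the trial past 80% power.* At 140 or so per arm, unstratified power near 80% requires a difference of about 0.165 (143 per arm), more than twice the stated 0.07.

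**Conclusion.** The point holds as a matter of efficiency. At the protocol's own effect and 140 evaluable patients per arm, stratifying the log-rank by clinical stage leaves power essentially unchanged if stage is not prognostic. It adds about 5 points at a hazard ratio near 2 per stage step, and about 10 points at a hazard ratio near 2.7. These gains rest on assumed stage effects, three equal groups and exponential hazards, none of which the documents supply. Power reaches about 34% at best (38% with 160 per arm). The sample size therefore needs its own correction, and the stratified test would remain worthwhile after it.

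**What to change.** Before database lock, and before any comparison of DFS by arm, write into the plan that:

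- the primary DFS test is a log-rank stratified by a few baseline stage groups built from cT and cN, with the groups and a rule for merging sparse ones fixed in advance;
- the hazard ratio comes from a Cox model stratified by the same groups and is described as a within-stage ratio;
- the plain log-rank is reported as supportive.

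Use clinical and not pathological stage. The number and station of nodes found in the specimen are themselves outcomes compared between the approaches, so pathological stage may depend on the arm.

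The change costs wording only: no new data, and no change to treatment or follow-up. The timing matters because the Study design section says that data analysts are not blinded, so strata chosen after the results are visible would carry little weight. If the full protocol or analysis plan already specifies this, the sponsor need only confirm it.

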## Discussion

Retrospecting from the past several decades, the incidence of AEG is showing an undoubted upward trend worldwide, and the incidence is also soaring faster than that of other parts of gastric cancer [28, 29]. AEG has a high recurrence and metastasis rate, leading to a poor prognosis [30]. Although the current comprehensive treatment including surgery, chemotherapy and targeted therapy can improve the prognosis to some extent, surgery is the only curable method for AEG [24], Nonetheless, the heated argument of the optimal surgical approach for AEG, particularly ST-II AEG (“true” carcinoma of the cardia) has been ongoing for more than three decades [12]. The treatment for thoracic surgeons usually complies with guidelines of esophagus carcinoma, the TA approach could ensure radical oncology resection for tumor margins and adequate lymphadenectomy, leading to a potential survival advantage [19, 31]. Abdominal surgeons usually consider the TH approach as a minor invasion and quicker recovery method [12, 32].

In the Netherlands, an RCT enrolled patients with Siewert types I and II AEG and compared the efficiency of the right transthoracic and transhiatal approaches. No significant difference was found between the two groups regarding hospital mortality and 5-year survival [33]. Another landmark large-scale RCT in Japanese included Siewert types II and III AEG, which compared the efficiency between the LTA and TH approaches. This trial was closed after interim analysis as the results showed the patients who underwent the LTA approach had more morbidity and no improvement in survival which confirmed in the 10-year follow-up [10, 12]. Recently, a systematic review and meta-analysis by Heger et al. showed that a higher rate of postoperative morbidity was associated with the thoracoabdominal approach for AEG patients compared with the transhiatal approach. However, the most significant limitation of this meta-analysis is the lack of relevant data focusing on ST-II AEG [9]. Recent work by Xing et al. retrospectively collected 211 Siewert type II AEG patients and compared the surgical approaches between the transhiatal and the right thoracoabdominal. As a result, the transhiatal group performed significantly better survival and fewer complications than that in the right thoracoabdominal group, as evidenced by propensity score matching (PSM) analysis [32]. Nevertheless, the credibility of these results should be treated with caution, as for the retrospective design and relatively small size.

To date, there have been no prospective randomized controlled trials regarding surgical therapy for ST-II AEG, leading to ongoing controversial debate for the optimal surgical approach. Our trial (S2AEG) will be the first RCT that focuses on ST-II AEG comparing the safety, feasibility and clinical efficacy between the TH with the RTA approaches. The successful implementation of this study will provide essential data on survival, oncological outcomes and QOL. The purpose of the S2AEG trial is to determine whether the TH or the RTA surgical approach is preferred for the ST-II AEG patients. The TH approach is expected to be equivalent to the RTA approach in terms of survival and oncological outcomes, while still offering an acceptable life quality at the same time. In brief, the results will provide high-level clinical evidence for clinical decision-making regarding the selection of a reasonable surgical approach for ST-II AEG.

## Data Availability

The study’s data and materials will be made accessible upon reasonable request.

## Abbreviations

AEG: Adenocarcinoma of the esophagogastric junction
EGJ: Esophagogastric junction
ST-II AEG: Siewert type II adenocarcinoma of the esophagogastric junction
TH: Abdominal-transhiatal
TA: Thoracoabdominal
RTA: Right thoracoabdominal
LTA: Left thoracoabdominal
QOL: Quality of life
RCT: Randomized controlled trial
LN: Lymph node
DFS: Disease-free survival
CT: Computer tomography
MRI: Magnetic resonance imaging
PET-CT: PET: positron emission computer tomography
ASA: American Society of Anesthesiologists physical status classification
ECOG: Eastern Cooperative Oncology Group
NRS: Nutrition Risk Screening
NYHA: New York Heart Association
FEV1: Forced expiratory volume in the first second
NRS-2002: Nutrition Risk Screening 2002
OS: Overall survival
EORTC: European Organization for Research and Treatment of Cancer
SD: Standard deviation
IQR: Interquartile range
PSM: Propensity score matching
